## Abstract

**Background:**

Currently 21% of the German population is older than 65 years. Above this age, the risk of suffering from chronic disease and mental disorders increases rapidly. Therefore, physical inactivity is one of the most important public health concerns among older people. To address this issue, we have conceptualised and evaluated a simple and low-threshold intervention, which requires only minimal demand on the participants, targeting older people with inadequate activity levels. The aim of the POWER Study is to investigate whether volunteer-supported outdoor-walking improves physical function and quality of life in older people.

**Methods/design:**

In a randomised, controlled interventional superiority-trial, individuals older than 65 years of age living in the community or nursing homes will be randomised into two groups. The study will be conducted in two study centres with assessments at baseline, 6 and 12 months. The intervention group will participate in a supported physical activity intervention for 6 months. An assigned volunteer will visit them three times a week for an outdoor walk between 30 and 50 min, or equivalent indoor activity. Persons in the control group will be invited to two lectures covering topics related to health. Primary endpoint is the physical function measured by the Short Physical Performance Battery (SPPB) at baseline, after 6 and 12 months. Secondary and safety endpoints will be quality of life (EQ. 5D), fear of falling (Falls Efficacy Scale), physical activity (activity diary), cognitive executive function (clock drawing test), falls requiring medical attention, hospitalisation and death. Primary analysis will be carried out by intention to treat.

**Discussion:**

We expect the intervention to improve the overall health status of the participants in a wide range of health-related outcomes. If effectiveness can be shown, the intervention will close an important gap in current services for older people. We will disseminate our experiences and results in the form of informational documents (training manual) to allow municipalities and health care organisations to implement a similar intervention.

**Trial registration:**

The trial was registered on 31 Aug 2018; German Clinical Trials Register (www.germanctr.de), Deutsches Register Klinischer Studien: DRKS00015188.

**Supplementary Information:**

The online version contains supplementary material available at 10.1186/s12877-020-01988-9.

## Background

Currently about 81 million people are living in Germany, of which 21% are older than 65 years [1]. While the total population will presumably increase to 82 million in the year 2040, the proportion of people older than 65 years will increase to 26% [2]. After the age of 65, the risk of suffering from 2 or more chronic diseases, metabolic conditions as well as the risk of falls increases rapidly [3]. The risk of falling also increases with age. More than 10% of all individuals between the age of 65 and 80 years have fallen more than once during the year prior to the interview [4, 5]. The more chronic diseases somebody experiences, the higher is the probability for mental health disorders (e.g. depression) [4]. A German population-based study showed that the odds for suffering from clinically depression are almost twice as high in people with four chronic diseases as compared to those with two [4].

To prevent the development or exacerbation of chronic diseases in older individuals, it is essential to maintain regular physical activity. While the World Health Organization (WHO) recommends at least 2.5 h of moderate physical activity per week [6], 73% of German women and 67% of German men above the age of 65 years do not meet this recommendation [7]. Therefore, physical inactivity is one of the most important public health concerns, especially in older people. Despite an increase in age-targeted activities offered by public health and community organisations, the proportion of people above 70 years who are sufficiently active is still below 14% [8]. Therefore, engaging means to stimulate sports and other physical activity are required.

To our knowledge, so far only a few studies examined the effects of a walking intervention on community dwelling individuals. A British mixed-methods study examined a sample of people between 60 and 75 years who were recruited in primary care practices [9]. This complex intervention included feedback by pedo- and accelerometers, scheduled practice nurse consultations and activity diaries to establish regular self-paced walking. There was an improvement in the primary outcome “daily step-counts” and the participants reported gains in health and wellbeing in the qualitative component of the study [9]. However, the quantitative component lacked these and other health related measures to back up the qualitative findings (e.g. physical function, quality of life). Other major limitations of the study are the need for qualified staff and expensive technological equipment [9]. An Australian study on community dwelling individuals aged 65+ years evaluated a self-paced 48 week walking programme that involved mailed printed manuals and telephone coaching [10]. The intervention successfully led to an increase in activity and physical function as measured by the Short Physical Performance Battery. In addition, the sample was relatively fit and lacked older individuals with mild and moderate limitations [10]. Another pilot study showed that a combination of initial motivation by a peer volunteer and subsequent activity such as walking in groups, yoga or dancing led to behavioural changes in older people and improved physical activity [11].

Taken together, these studies show that interventions aimed at promoting regular walking improve older persons’ health. However, the interventions were complex and required professional input. Moreover, individuals who already had physical, sensory and/or cognitive limitations were not or not sufficiently included in the community dwelling studies.

The aim of the POWER Study is to investigate whether volunteer-supported outdoor-walking improves the physical function and quality of life of older people. A further aim is the implementation of the intervention in existing aid structures (e.g. regional health department). The POWER Study design has been conceptualised and piloted [12] as a simple and low-threshold intervention that is targeted at older people with inadequate activity levels, already present minor restrictions in physical and mental functioning preventing them from self-paced physical activity, and a lack of support.

## Methods/design

We are carrying out a randomised, controlled interventional superiority-trial with two parallel groups with physical function as primary endpoint to examine whether volunteer-supported walking interventions for older people improve physical health. Measurements will be done at baseline (T0), at 6 months (T1) and at 12 months (T2) (see Table 1).

**Table 1 Tab1:** Measures use for the assessments

Outcome Measure	Operationalisation (Type of assessment)	Times of assessment		
		T0	T1	T2
**Participant**				
Sociodemographic Data	Age, sex, level of care, family status, education level, ethnicity	X		
Physical Function	Short Physical Performance Battery	X	X	X
Quality of Life	EQ-5D-5L	X	X	X
Fear of Falling	Falls Efficacy Scale	X	X	X
Frailty	Clinical Frailty Scale	X	X	X
Cognitive Changes	Clock-drawing-test	X	X	X
Cognitive Impairment	Mini Mental Status Examination (MMSE)	X		
Walk Assessment	Number and duration of walks, assistance, type of assistance		X	X
Falls	Type and place of treatment		X	X
Treated Falls	Date, ICD Code, falls		X	X
Hospitalisation	Date of hospital admission and discharge, duration of hospitalisation, reason for hospitalisation (ICD-10-Code)		X	X
Death	Date of death, Reason for death (ICD-10-Code)		X	X
**Volunteer**				
Sociodemographic Data	Age, sex, job, family status, education level, ethnicity, volunteering history			

### Aims

Our research questions are:
Compared to controls, does volunteer-supported walking improve physical function and quality of life as well as lower fear of falling? Furthermore, improves supported walking the cognitive executive function and the general physical activity? [Effectiveness]Compared to controls, does volunteer-support walking increase the rate of falls needing medical attention, rate of admissions to hospital, duration of hospitalisations and mortality? [Safety]Compared to controls, does supported walking have an impact on the frequency and duration of hospitalisations and/or mortality? [effectiveness, safety]

Finally, we explore whether the intervention can be successfully implemented into existing community services.

### Setting

A cohort of participants 65 years and older from North Rhine-Westphalia (Germany) and Hesse (Germany) will be recruited and followed up for 12 months. Participants will be recruited from nursing homes and from the community setting including general practitioners and home care nursing services.

### Eligibility

Eligibility criteria will be assessed at baseline.

Inclusion criteria:
People aged ≥ 65 yearsReduced physical function (Short Physical Performance Battery Score (SPPB [13];)< 9 at baseline)Not confident to go for a walk on their own

Exclusion criteria:
Not giving informed consentMini-mental status examination (MMSE) score at baseline < 18 [14]Insufficient physical function to allow for volunteer-supported walking with adequate safety (SPPB at baseline ≤2 in nursing homes and ≤3 in the community setting)Excellent physical function making it improbable that participants will benefit from the intervention (SPPB-Score ≥10)Permanently bedriddenCan only be mobilised in a wheelchairRegular physical activity levels at least equivalent to the intervention (> 150 min/week)Life expectancy of less than 6 monthsOther foreseeable inability to take part in the intervention for 6 monthsKnown alcohol or drug addiction or active psychosis during the last 12 monthsAnother person of the same household participating in the study

Individuals using a walking frame, a cane or a wheeled walker will be included, as well as those suffering from Parkinson’s disease or mild cognitive impairment (MMSE ≥18). We expect all of these to benefit from the intervention, and we presume that volunteers will be able to cope with these disabilities or restrictions.

Eligibility criteria will be communicated to recruiting organisations, such as nursing homes or primary care practices. The final decision regarding eligibility will be made at the baseline examination, since some in- or exclusion criteria are formally assessed on this occasion, such as cognitive or physical function.

### Volunteers

Cooperating partner organisations (e.g. volunteer agency) will recruit volunteers. Advertisements in local newspapers, internet forums and bulletin boards (e.g. of universities and schools) will also be used. The minimum age will be 16 years, which is the minimum age for helpers in the federal volunteering service (Bundesfreiwilligendienst), and the possession of a mobile phone. Sufficient proficiency in German, sufficient self-reported physical fitness to be able to assist and availability for at least 6 months will be required. The number of participants assigned to one volunteer will be based on his/her time available and the physical condition of the participants.

The training is scheduled to take 6 h and includes instructions with regards to assisting older people (e.g. handling of tools like wheeled walker) and the documentation of the walks. Afterwards, volunteers will be assigned to the participants. Preferences will be taken into account (e.g. assistance a female person, participant living near home). They will be instructed to schedule the appointments with the participants themselves.

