### Randomisation

Participants will be randomly assigned to either control or experimental group with a 1:1 allocation as per computer-generated randomisation schedule stratified by setting (community [primary care practice, nursing services] or nursing home). Participants will be randomly allocated via a telephone service provided by the Clinical Trial Centre at the University of Marburg (Koordinierungszentrum für klinische Studien [KKS]).

Research assistants will perform the data collection and examinations at baseline (T0) after 6 months of the intervention (T1) and after 12 months of follow up (T2). They will visit each participant either at their home or care home.

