### Study procedure and intervention

After baseline assessments (T0) and randomisation, individuals in the intervention group will participate in a supported physical activity intervention for 6 months. They will be visited by an assigned volunteer three times a week to go for a walk outdoors. The duration of the walk will depend on the participant’s physical ability. The aim is to gradually increase walking duration to three times 50 min to meet the WHO recommendation of 150 min per week [6]. In case of bad weather, the activity can take place indoors and will consist of exercises for balance and strength based on a programme of the federal centre for health education [15]. Each participant and his/her volunteer together will keep an activity diary, noting the date, time, duration and type of each activation exercise (outdoors or indoors). Events relevant for safety, e.g. falls or injuries, will also be recorded. Furthermore, after each walk, the subjectively experienced physical strain of the walk will document by a visual analogue scale.

Participants in the control group are invited to two lectures covering topics related healthy ageing during the 6 months of the intervention. The presentations will be in an easy to understand and entertaining manner and address health related topics for older people, e.g. nutrition. After 6 months of intervention the post intervention examination will take place (T1). We will evaluate the effect of the intervention in comparison with the control group. Study participants in both groups will be followed for another 6 months until the 12 months final examination (T2). During this period, the study centres will neither provide nor coordinate any walking service. However, we expect the collaborating partners and other community services to continue providing support for regular walking as initiated during the first 6 months of the study.

The evaluation of the extended period at T2 has two main objectives. First, to prolong participants’ follow-up and to assess long-term effects of regular walking (up to 12 months) and second, to evaluate potential sustainability and dissemination of the study intervention after cessation of support from the study centres (Fig. 1).

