#### Data analysis

At T1, we will apply an analysis of covariance of the primary outcome physical function (SPPB scores). This outcome will be used to analyse the difference between the intervention and control group. In case of non-normally distributed data, we will apply a nonparametric covariance model [34]. The secondary outcomes will be evaluated with ANCOVAs, t-tests or distribution independent Mann-Whitney U-Tests. To compare the number of deaths, events leading to discontinuation of the intervention, falls requiring medical attention, and hospital treatments, we will either calculate a χ2-test, Fisher exact test for binary variables or conduct a log-rank-test. Since the number of falls or falling in general has shown to depend on fear of falling and the amount of physical activity, we will perform a mediator analysis to correctly identify the effect of our intervention on falling [35].

Furthermore, we will perform exploratory analyses (multifactorial ANCOVAs and in case of non-normally distributed data adjusted rank transform tests [36]) and dichotomise and evaluate whether the participants in the subgroups setting (community setting, nursing home), sex, rural/urban setting, frailty, and baseline SPPB score show different results in our primary outcome SPPB or in secondary outcomes. We will perform this analysis at T1 and T2.

The evaluation of the intervention will be performed as intention-to-treat (ITT). The ITT analysis will include all randomised participants irrespective of the actual performance of the intervention. In case a participant decides to withdraw consent, we will ask for a final evaluation.

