## Discussion

This current paper presents the study protocol of a randomised, controlled interventional superiority study: the POWER study. This project targets older people with inadequate activity levels. With this study, we will evaluate a volunteer-supported physical activity intervention and expect this intervention to improve the overall health status of the participants in a wide range of health-related outcomes.

This is a pragmatic study evaluating the effect of an intervention consisting of three components: 1) motivation by another person; 2) physical assistance; 3) psycho-social support (company). The control treatment does not address these mechanisms directly but aims to keep participants interested and motivated to comply with study procedures.

This study includes some limitations. Despite the fact that participants are recruited through a range of different settings, there is a possibility of selection bias, as participants have to be willing to complete the intervention. Participants who do not participate may be more isolated, less active and have more health issues than the participants included in the study. Furthermore, selective attrition due to death and geographical mobility of participants is possible. As mentioned above, blinding of participants and the research team is impossible to achieve.

We propose and evaluate a simple, personal non-educational intervention that is addressing the problem of physical activity in the group of already physically restricted older people with a lack of social support. In our opinion, it is well suited for a wide range of individuals with widely differing educational and/or socioeconomic backgrounds. In addition, participants with language barriers, who would be left out of many educational programmes, will be able to participate in the same way as other participants. The intervention provides a realistic way to motivate older people to become physically more active. Not relying on professional input, it requires limited financial or staff resources. The fact that the service will be provided personally by volunteers, will increase participants’ motivation and improve their quality of life.

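### Volunteers may be shared within the intervention arm, but the T1 ANCOVA and the sample size treat participants as independent; if volunteers differ in their effect, the standard error of the treatment contrast is somewhat too small

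*Protocol article*

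**What the plan says.** All places are in the protocol article.

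- **Randomisation** is by individual: "Participants will be randomly assigned to either control or experimental group with a 1:1 allocation", stratified by setting.
- **Study procedure and intervention** gives volunteers to one arm only. Of the intervention group it says: "They will be visited by an assigned volunteer three times a week to go for a walk outdoors". Of the controls: "Participants in the control group are invited to two lectures covering topics related healthy ageing during the 6 months of the intervention".
- **Volunteers** leaves the caseload open: "The number of participants assigned to one volunteer will be based on his/her time available and the physical condition of the participants". Matching is not random: "Preferences will be taken into account (e.g. assistance a female person, participant living near home".
- **Discussion** lists three components of the intervention, the first being "motivation by another person"; the other two are physical assistance and company. The volunteer delivers all three.
- **Data analysis** sets the primary model: "At T1, we will apply an analysis of covariance of the primary outcome physical function (SPPB scores". A nonparametric covariance model is the fallback, and Missing data adds worst-rank scoring for death or admission.
- **Sample size** derives 103 per group from a 1-point difference, SD 2.8, R-square 0.5 for the baseline covariate, 5% significance and 95% power. It inflates 206 to 345 for 40% loss, with 230 planned from the community and 115 from nursing homes.

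Neither Sample size, Data analysis nor Missing data mentions a volunteer effect, an ICC, a design effect or a clustered variance.

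**The concern.** Participants who share a volunteer share the person who delivers the treatment. If some volunteers achieve more than others, T1 scores within a volunteer are positively correlated in the intervention arm, with no counterpart in the control arm. An ordinary ANCOVA ignores that extra variance. Adjustment for baseline SPPB does not remove it, because it arises after randomisation. Stratification by setting does not remove it either, because volunteers exist in one arm only.

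At stake are a confidence interval somewhat too narrow and a p-value somewhat too small for the primary comparison of a superiority trial, together with a stated power that is slightly optimistic. A larger sample would restore power. It would not remove the type I inflation, which at a given caseload and ICC stays the same.

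**Working it through.** **Inputs from Sample size:** difference 1 point (the SD of the two means is 0.50), SD 2.8, R-square 0.5, two-sided 5%, 103 per group, 40% loss, 345 in total, of whom 115 from nursing homes.

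**Assumed, because the document gives neither:** m participants per volunteer, 1 to 5; ICC 0.02 to 0.10 on the baseline-adjusted outcome.

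**Step 1. Reproduce the plan's figure.** Residual SD = 2.8 × √(1 − 0.5) = 1.980. The noncentral F test with 2n − 3 error degrees of freedom gives 94.84% power at n = 102 and 95.03% at n = 103. So 103 per group is exactly what independence gives, with no allowance for clustering. The inflation is 206 / 0.6 = 343.3, or 344, against 345 stated; this is close enough.

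**Step 2. Clustering in one arm.** The variance of the intervention mean is multiplied by DE = 1 + (m − 1) × ICC; the control arm is unchanged. The standard error of the contrast therefore grows by k = √((1 + DE) / 2).

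- Independent SE: 1.980 × √(2/103) = 0.2759.
- Actual type I error of the unadjusted test: 2 × [1 − Φ(1.96 / k)].
- Power: Φ(1 / (0.2759 × k) − 1.96).

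With k = 1 this normal approximation gives 95.2% power.

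| m (whole arm) | ICC | DE | k | Type I error | Power |
|---|---|---|---|---|---|
| 1 | any | 1.00 | 1.000 | 5.0% | 95.2% |
| 2 | 0.02 | 1.02 | 1.005 | 5.1% | 95.0% |
| 2 | 0.05 | 1.05 | 1.012 | 5.3% | 94.7% |
| 3 | 0.05 | 1.10 | 1.025 | 5.6% | 94.3% |
| 3 | 0.10 | 1.20 | 1.049 | 6.2% | 93.3% |

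**Step 3. A heavier caseload in nursing homes only.** Nursing homes supply 115 / 345 = one third. With m = 5 there and m = 1 or 2 elsewhere, the average DE is (1/3)(1 + 4 × ICC) + (2/3)(1 + (m − 1) × ICC).

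| m elsewhere | ICC | Average DE | k | Type I error | Power |
|---|---|---|---|---|---|
| 1 | 0.05 | 1.067 | 1.016 | 5.4% | 94.6% |
| 2 | 0.05 | 1.100 | 1.025 | 5.6% | 94.3% |
| 1 | 0.10 | 1.133 | 1.033 | 5.8% | 93.9% |
| 2 | 0.10 | 1.200 | 1.049 | 6.2% | 93.3% |

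**Step 4. Check by simulation.** With 103 per arm and 40,000 runs, the unadjusted test rejected in 4.9% (m = 1), 5.3% (m = 2, ICC 0.05), 5.7% (m = 3, ICC 0.05) and 6.2% (m = 3, ICC 0.10). The formula holds. Unequal caseloads, which the Volunteers section implies, would raise DE somewhat.

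**The case against.** Several points on the other side stand, and they limit the claim.

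- **It is conditional.** A reader might infer that the standard error simply is too small. The document does not support that. It needs both shared volunteers and volunteers who differ in their effect, and neither the caseload nor the ICC is given.
- **Type I error needs care.** If walking with a volunteer changes nothing for anyone, volunteers create no correlation and there is no inflation. The figures above apply when effects differ between volunteers but average to zero. Similarity from living in the same home or district is present in both arms and does not invalidate an individually randomised comparison.
- **The evidence for a positive ICC is indirect.** The Discussion describes components common to the whole intervention, not differences between volunteers, and training and visit schedule are common to all. Against this, volunteers may be as young as 16, have 6 hours of training and arrange the appointments themselves, so some variation in delivery is plausible.
- **A heavy caseload across the whole arm is not supported.** Five per volunteer throughout, with ICC 0.10, would give 7.4% type I error and 91% power, and a reader might take that as the size of the problem. But nursing homes supply only 115 of 345, and five participants at three visits each means 15 visits a week for six months.
- **Power refers to 103 per arm.** The intention-to-treat analysis keeps all randomised participants by scoring or imputing missing values, so the analysed number is nearer 172 per arm (345 / 2), with a different outcome distribution.

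It can also be said that a statistical analysis plan, not shown, may add a volunteer term. It may; but the published sample size makes no allowance, and the primary model is named here without one.

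**Conclusion.** The concern holds in conditional form. The design is partially nested, and neither the named primary model nor the sample size allows for it. If volunteers are shared and differ in their effect, the standard error of the treatment contrast is understated by up to about 5% over the ranges tabulated: type I error about 5.1 to 6.2% instead of 5%, and power at 103 per arm about 93 to 95%. If each volunteer serves one participant, nothing is lost. The caseloads and ICCs are assumptions, not figures from the document. The effect is modest and does not threaten the trial, but its direction is known once the conditions are met, and it can be corrected cheaply before the data are analysed.

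**What to change.** 1. Record the volunteer ID for each intervention participant and keep it in the analysis data.
2. Pre-specify that the standard error of the T1 comparison, including any rank-based version, is clustered by volunteer, with each control as a singleton and a small-sample correction. This suits small clusters and tied worst-rank scores better than a compulsory Gaussian random-intercept model. At minimum, report it as a pre-specified sensitivity analysis.
3. Describe the 95% power as assuming no volunteer clustering.

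The cost is a change of analysis wording, one data field and a slightly wider interval. There is also a cost to blinding. The Blinding section gives the statistician group numbers only, and an ID present in one arm can reveal which arm is the intervention. The model code should therefore be fixed before the ID is merged. The conflict is not new: the per-protocol rule under Missing data already requires walk attendance from the intervention arm alone.
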